**Table 3.3. Summary on source of questionnaire that will be adopted and adapted from previous study**

| Section                                  | Source of questionnaire adaption | Number of items |
|------------------------------------------|----------------------------------|-----------------|
| Section D: Knowledge of hepatitis C      | (Arain et al., 2016)             | 19 items        |
| Section E: Attitude towards behaviour    | (Chen et al., 2013)              | 10 items        |
| Section F: Subjective norm               | (Francis et al., 2004)           | 4 items         |
| Section G: Perceived behavioural control | (Francis et al., 2004)           | 4 items         |

## 1.11 Quality Control of the study Instruments

### 1.11.1 Quality control of the Health Education Intervention Module

The developed health education intervention module will be subject to pretesting prior to the full-scale intervention study. The pretest will be conduct among the MMT client that will be exclude from the main study. The objective of pretesting is to obtain feedback from the respondent about the module, to assess the feasibility in implementing the module, and to improve the newly developed health education module. Feedback such as weather the content of module were easily understood, cultural acceptance, flow of the training, resources required in implementing the module (e.g.: time, equipment’s, suitability of the person delivering the material, budget), hiccups in implementing, intervention adherence will be assessed to improve the health intervention module.

In addition, the health education module will also be subject to assessment by healthcare provider using the Patient Education Materials Assessment Tool (PEMAT) (Shoemaker et al., 2014). This method is a systematic method to evaluate and compare the understandability and actionability of patient's education material with aim to produce a high-quality material to patient.

After correction of the module based on feedback form pretest assessment, the module will be implemented in the pilot testing, which is small-scale, preliminary study which aim to investigate whether the health intervention module is feasible before conducting in a larger scale interventional study.

#### **1.11.2 Quality control of the Questionnaire**

All scale that will be use in this study were adopted from previous study conducted in different countries. Thus, the scale will be translated from English language to Malay language based on the report of the ISPOR Task Force for Translation and Cultural Adaptation (TCA) (Wild et al., 2005). First, forward translation from English to Malay language will be conducted by two translator who were Malay native speaker and proficient in English language. Subsequently, both translators will synthesis the Malay translated version of the questionnaire. Next the two scale will be compared and undergo reconciliation in which any discrepancies will be resolved to obtain a single forward translated version of the scale. Following that, another two translator who have not seen the original questionnaire will be invited to back translated the forward translated version of the scale into original language which is English. Next, the back translated version of questionnaire will be review against the original questionnaire to ensure conceptual equivalence of the translation. Next is the harmonization step in which all version of translation will be compare with the original version of questionnaire to detect and deal with any translation discrepancies that arise between different language versions, thus ensuring conceptual equivalence between the source and target language versions and between all translations.

Subsequently, the translated version of questionnaire will be test in the pretest study to perform the cognitive debriefing of the questionnaire with the aims to assess the level of comprehensibility and cognitive equivalence of the translation, to test any translation alternatives that have not been resolved by the translators and to highlight any items that may be inappropriate at a conceptual level. After correction and finalizing the scale, pilot study will be carried out before the full-scale intervention took place.

##### **1.11.2.1 Face Validity**

Face validity of the instrument was performed to evaluate the appropriateness of the phrasing and understanding of the items. It was conducted among two lecturers and three students of the Doctor of public health of Universiti Putra Malaysia (UPM). Subsequently, based on the comments and feedback for improvement by the individuals, the needed modification will be considered.

##### **1.11.2.2 Content Validity**

The content validity of questionnaire will be assessed by a group expert. This evaluation will be performed by six experts, which include three public health physicians and three family medicine physicians. The content validation ratio (CVR) will then calculated using formula from a previous study (Lawshe, 1975). Items with a value lower than 0.99 were either eliminated or modified based on the importance of

the items. Furthermore, the comments and feedback by the panel of experts will be taken into consideration for further correction of the questionnaire.

In addition, the Content validity index (CVI) will be calculated to assess the relevance and clarity of the questionnaire by the assigned expert. Following that, the Item CVI (I-CVI) and the scale average CVI (S-CVI/Ave) will be calculated. Polit et al., (2007) recommended a value of 0.78 or higher for I-CVI and 0.90 or higher for S-CVI/Ave to judge a scale as having excellent content validity. The questionnaire will then be modified according to the agreement level of the expert based on the calculated CVI.

#### **1.11.2.3 Reliability**

The reliability of the instrument will be assessed using internal consistency, calculated in IBM SPSS (Version 28). Sample size for the reliability test will be determined using an online calculator ([https://wnarifin.github.io/ssc\\_web.html](https://wnarifin.github.io/ssc_web.html)), and MMT clients will be recruited accordingly. These participants will not be included in the main study.

Cronbach's alpha will be used for Likert-scale items, while Kuder-Richardson 20 will be used for dichotomous items. Both methods are recognised as valid for assessing internal consistency (Capik & Gozum, 2015). While a Cronbach's alpha value of  $\geq 0.70$  is commonly accepted as satisfactory, some literature allows values as low as 0.45 (Taber, 2018). For Kuder-Richardson 20, a value of 0.50 or higher is considered acceptable.

#### **1.11.2.4 Training of the Enumerators**

Training of the enumerators will be conducted prior to commencement of the intervention. A medical officer in charged for Methadone program from each selected clinics will be appointed as the liaison officer in charge of data collection and distribution of the intervention packages (health talk and video). They will also be responsible for consent form distribution and collection. They will be train on how to conduct the health talk and response to enquiry regarding content of the intervention module.

### **1.12 Implementation of the Health Education Intervention**

An intervention module based on the Theory of Planned Behaviour (TPB) will be delivered to the intervention group through a 20 to 30 minute face-to-face session during routine MMT clinic appointments. Conducted by trained medical officers, the intervention will take place over four months and involve randomly selected MMT clients from government clinics in Malacca.

The session includes three parts: a health talk to improve knowledge and attitudes about hepatitis C; a pre-recorded video of a patient who completed DAA treatment, aimed at enhancing subjective norms; and another video addressing common barriers to treatment.

Before implementation, medical staff will undergo training on delivering the module and conducting interviews. Participants will complete a baseline survey, followed by assessments immediately after the intervention and three months later. The control group will receive the same intervention after the final data collection.

### **1.13 Data collection process**

At the start of the study, clients were randomly selected from the sampling frame and allocated into intervention and control groups. A liaison officer was appointed from each clinic with selected participants and was trained on the study procedures. Eligible clients were approached for consent, and baseline data were collected from those who agreed to participate.

Participants in the intervention group received an intervention package within one to two weeks. The session lasted approximately 30 minutes and included a health talk on hepatitis C and a video featuring a patient sharing their experience with DAA treatment. Outcomes were assessed immediately after the intervention (T1) and again three months later (T2). The control group completed the same assessments at baseline, one to two weeks after baseline (T1), and three months after T1 (T2). After the final assessment, the same intervention package was provided to the control group.

### **1.14 Study Variables**

#### **1.14.1 Dependent Variables**

##### **1) Primary outcome**

The primary outcome of this study will measure the willingness of the clients for hepatitis C treatment following diagnosis of hepatitis C

##### **2) Secondary outcome**

The secondary outcome of the study will be the score of knowledge on hepatitis C, the score of attitudes towards hepatitis C infection, the score of subjective norms and the score on perceived behavioural control

#### **1.14.2 Independent Variables**

##### **Hepatitis C Health education intervention**

This is the exposure variable of interest in this study. The module will be delivered to the intervention group during the study and to the control group at the end of the study (wait list) if the intervention we found to be effective.

#### **1.14.3 Other Factors Associated with the Primary and Secondary Outcomes**

- i. Sociodemographic
  - a. Age
  - b. Gender
  - c. Race
  - d. Marital Status
  - e. Employment status
  - f. Monthly income
  - g. Education level
- ii. Duration of MMT
- iii. Alcohol and drug use history
- iv. HIV status
- v. Hepatitis C status
- vi. History of attending Hepatitis C program

### **1.15 Data Analysis**

#### **1.15.1 Statistical Test in Data Analysis**

Data collected will be analysed using IBM SPSS (Version 27.0). Data exploration will be performed to look for any error in data entry, missing data and presence of outliers.

The distribution of numerical data will then be determined whether they are normally or not-normally distributed. In determining the normality of data both statistical and graphical method will be use. For statistical method, the Skewness/SE of skewness and the Kolmogorov-Smirnov parameter will be calculated, while for the graphical method, the histogram together with stem and leaf box plot will be plotted and analyses. Furthermore, after determining the normality of data, mean and standard deviation will use to described normally distributed data, while median with first and third quartile (Q1, Q3) will be used to described not normally distributed data. Categorical data will be presented as frequency and percentage.

For between group comparison, the independent sample t-test will be used to compare the mean different of continuous and normally distributed data between intervention and control group. For continuous but not normally distributed data, the Mann-Whitney U test will be used to compare between intervention and control group. The Chi-square test will be used to compare frequency different of categorical data between intervention and control groups and for data of 2 by 2 table that contains cell with an expected count less than 5 for more than 20%, the Fisher's exact test will be use.

For within group changes overtime comparison, the One-way repeated measure ANOVA will be used for continuous and normally distributed variables. Within group analysis for categorical data will use the Cochran's Q test.

The Generalized Linear Mixed Model (GLMM) will be used to test the main effect and interaction between and within the intervention and control groups overtime (baseline, immediately post intervention, and 3-month post intervention). This study will use a significance level with a *p*-value of 0.05 and a confidence interval of 95% for hypothesis testing. For results yielded *p*-value of less than 0.05 will be consider as statistically significant findings.

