**Table 3.1. Information for sample size calculation**

| Study Characteristic | Assumption made by investigator                                                                                                                        |
|----------------------|--------------------------------------------------------------------------------------------------------------------------------------------------------|
| Type of study        | Randomize Control Trial                                                                                                                                |
| $Z_{(1-\alpha/2)}$   | $Z_{(1-\alpha/2)} = 1.96$ , the value of the standard normal distribution corresponding to a significance level of alpha of 0.05 for a two-sided test. |
| $Z_{(1-\beta)}$      | $Z_{(1-\beta)} = 0.842$ , the value of the standard normal distribution corresponding to the desired level of power of 80%.                            |
| $P_1$                | $P_1 = 0.75$ , Proportion of respondent willing for treatment in intervention group at 3 months post intervention                                      |
| $P_2$                | $P_2 = 0.44$ , Proportion of respondent willing for treatment in control group at 3 months post intervention                                           |
| $\bar{P}$            | $\bar{P} = (0.75 + 0.44) / 2$ , $\bar{P} = 0.595$                                                                                                      |

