### 1.10.2 Questionnaire

Questionnaire that will be use is a self-administered questionnaire that will be distributed to respondent in Malay language. Estimated duration to answer the questionnaire is 20 minutes. The questionnaire section related to knowledge of hepatitis C and construct of TPB will be adopted from previous study. The validity and reliability assessment of the questionnaire will be discussed in respective sections. The set of questionnaires for this study will contain

- i. Section A for Sociodemographic characteristics  
This section will ask regarding respondent sociodemographic characteristics which include age, gender, race, marital status, employment status, monthly income, and education level.
- ii. Section B for MMT treatment profile  
This section will explore regarding history of MMT treatment which include current Methadone dose in mg/day and duration of MMT treatment in years.
- iii. Section C for HIV and Hepatitis C status  
This section will explore regarding respondents HIV and hepatitis C screening history and current HIV and hepatitis C status.
- iv. Section D for history of hepatitis C educational program  
This section will explore regarding respondents' history of attending any hepatitis C educational program.
- v. Section E for substance use history  
This section will explore regarding history of smoking and history of ever and past 6 month injecting and non-injecting drug use as well as alcohol use history among the respondents.
- vi. Section F for willingness for hepatitis C treatment  
This section will explore regarding respondent willingness for hepatitis C treatment is they were diagnosed with hepatitis C and offered for treatment. Respondent will need to select between yes or no to indicate their willingness for hepatitis C treatment.
- vii. Section G for knowledge of hepatitis C  
This section will explore regarding respondent knowledge on hepatitis C infection, transmission, prevention, and treatment. The questionnaire in this section will be adopted from previous study by Arain et al., (2016). Total item in this scale are 19 items. The answer options will be "True", "False" and "Not sure". Each answer will be given 1 mark for "yes" answer and 0 for "no" and "don't know" answer. Total score will range from 0 to 19 and the higher the score reflect higher knowledge of respondent on hepatitis C infection.
- viii. Section H for attitude towards hepatitis C infection and treatment  

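### The normality check that picks the test for the four secondary scores has no decision rule, and neither test it can pick uses the baseline score already collected

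*Protocol*

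**What the plan says.** The four secondary outcomes (section 1.14.1) are sums of questionnaire items, so each takes whole-number values only. For knowledge, section 1.10.2 states "Total score will range from 0 to 19". The other ranges are 10 to 50 for attitude and 4 to 28 each for subjective norm and perceived behavioural control. All are measured at baseline, T1 and T2 (sections 1.12 and 1.13).

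Section 1.15.1 first classes numerical data as normal or not. On the statistical side, "the Skewness/SE of skewness and the Kolmogorov-Smirnov parameter will be calculated"; a histogram and a stem-and-leaf or box plot are added. The class then fixes the analysis:

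- Between groups, data judged normal go to the independent t-test. Otherwise: "For continuous but not normally distributed data, the Mann-Whitney U test will be used to compare between intervention and control group".
- Within groups, "the One-way repeated measure ANOVA will be used for continuous and normally distributed variables". Cochran's Q is named for categorical data. Nothing is named for a continuous score judged non-normal.

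The same section also plans a generalized linear mixed model (GLMM) over the three visits, with group, time and their interaction. It does not depend on the normality check.

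**The concern.** H2 to H5 and specific objective iv call for between-group comparisons of four scores at two post-intervention visits, so eight comparisons pass through the check. Its criteria have no thresholds and no order of precedence, so the choice of test is left open until the outcome data have been seen. One scale could be compared by means at T1 and by ranks at T2, with no common effect estimate.

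Two further gaps sit beside this. Neither between-group test uses the participant's own baseline score. And where the gated test and the GLMM differ, the protocol does not say which one answers the hypothesis.

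**Working it through.** **Planned size.** Table 3.1 gives Z = 1.96 ("corresponding to a significance level of alpha of 0.05 for a two-sided test"), Z = 0.842 ("corresponding to the desired level of power of 80"), P1 = 0.75 ("Proportion of respondent willing for treatment in intervention group at 3 months post intervention") and P2 = 0.44 ("Proportion of respondent willing for treatment in control group at 3 months post intervention"). With mean proportion 0.595:

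n = {1.96 × √(2 × 0.595 × 0.405) + 0.842 × √(0.1875 + 0.2464)}² / 0.31² = (1.361 + 0.555)² / 0.0961 = 38.17, rounded up to 39 per arm.

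This reproduces the protocol's 39. It concerns the binary primary outcome; no power is stated for the scores. Section 1.7.6 inflates to 118 per arm (236 in all). It states 77% attrition but divides by 0.33, so the number left at the end would be 118 × 0.23 = 27 or 118 × 0.33 = 39 per arm.

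**How the normality criteria behave.** The protocol gives no SDs, so these are assumed: knowledge 2-4, norm and control 2.5-5, attitude 4-8. Normal values were rounded to integers and limited to each scale's range, with 1,000 runs per setting (Monte Carlo error at most 1.6 points). Rejection at 5% by Kolmogorov-Smirnov with estimated mean and SD (Lilliefors):

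| Score | n = 27 | n = 39 | n = 118 (one arm) | n = 236 (pooled) |
|---|---|---|---|---|
| Knowledge | 12-41% | 16-62% | 55-100% | 95-100% |
| Norm, control | 9-30% | 11-42% | 35-97% | 75-100% |
| Attitude | 6-13% | 8-19% | 14-54% | 32-95% |

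Truly continuous normal data are rejected in 3-5% of runs, so the excess comes from the integer scale. On integer scores, |skewness/SE| > 1.96 occurs in about 1-11% of runs, depending on the settings. The two numerical criteria will therefore often disagree. Without the Lilliefors correction, and at mid-range SDs, rejection at n = 118 and n = 236 is 7% and 47% for knowledge, 3% and 25% for norm, and 0.2% and 1% for attitude.

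**What the choice of test costs.** A 4-28 score with SD 3.5 was simulated, 3,000 runs per setting. The shift was set so that the t-test has about 80% power: 0.364 SD at 118 per arm, from (1.96 + 0.842) × √(2/118) ≈ 0.365. The correlation r between baseline and follow-up is assumed.

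| r | t-test | Mann-Whitney | Baseline-adjusted | Change score |
|---|---|---|---|---|
| 0.3 | 80.0% | 78.1% | 82.9% | 65.2% |
| 0.5 | 79.6% | 77.3% | 89.4% | 77.3% |
| 0.7 | 79.7% | 76.8% | 96.9% | 94.3% |

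At 39 per arm, with a shift of 0.635 SD, the pattern is the same: t-test 79-80%, Mann-Whitney 77-78%, adjusted model 82.5%, 87.8% and 97.1%.

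Analytic check: adjustment multiplies the variance by 1 − r² (0.91, 0.75, 0.51), so power is Φ(2.802/√(1 − r²) − 1.96) = 83.6%, 89.9% and 97.5%.

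The differences are:

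- Moving from the t-test to Mann-Whitney: 2-3 points lost.
- Leaving out baseline: about 3, 10 and 17 points lost against the t-test.

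With no true effect, the t-test, Mann-Whitney and adjusted model each reject in 4.5-5.7% of runs. Letting Kolmogorov-Smirnov pick the test gives 4.4-6.2%, the same as the t-test alone.

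**The case against.** The strongest reply is that the GLMM in the same section already includes the baseline visit and is not gated, so H2-H5 need not rest on the gated tests, and a score judged non-normal still has a within-group analysis. That is correct, and it rules out saying that the plan has no analysis using baseline. It leaves open which analysis decides. Including baseline as one of three outcome visits is also not the same as adjusting for it: the arm-by-time contrast from baseline is in essence a comparison of changes, and the last column of the power table shows that this can be weaker than the plain t-test when r is low.

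A reader might infer that the check will send most well-behaved scores to the rank test. The protocol does not support this. Kolmogorov-Smirnov is one criterion among several, nothing says it overrides skewness or the plots, the Lilliefors form is an assumption, and the high rates need the recruited 118 per arm. At 27-39 per arm most settings fall to about 10-30%.

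A reader might also infer that the check distorts the error rate or that the rank test is what loses power. Neither holds: Type I error stays near 5%, the two tests agreed on significance in about 98% of runs with no true effect, and the t-test ignores baseline just as the rank test does.

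Finally, covariates are often left to a SAP. But this protocol itself fixes the gate and the unadjusted tests, so the wording can be judged as it stands.

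**Conclusion.** The point holds as one of efficiency and clarity for the secondary outcomes, not of validity. Section 1.15.1 selects the between-group test from the data by criteria that have no rule and will often conflict on integer scores. Both possible tests discard the baseline score, at a cost of about 3 to 17 power points against a t-test with 80% power. A score judged non-normal has no named within-group test apart from the GLMM, and no analysis is named as deciding H2-H5.

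The sizes rest on assumed SDs, assumed correlations of 0.3 to 0.7, rounded normal scores and independent participants. The direction does not depend on the exact values: with any non-zero correlation, adjustment gains precision apart from a negligible loss of degrees of freedom.

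**What to change.** In section 1.15.1:

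1. Stop using the normality check to select the outcome analysis. Keep it, if wanted, for choosing mean or median in descriptive tables.
2. Name the mixed model as the deciding analysis for each of the four scores: outcomes at T1 and T2; terms for arm, time and arm by time; baseline score as covariate. Report the adjusted mean difference with 95% CI at each visit.
3. Label the t-test or Mann-Whitney result as descriptive.
4. For the within-group objective, use the three-visit mixed model already planned for every score, whatever its distribution.
5. Check residuals by plot, and give a bootstrap interval as a sensitivity analysis if they are skewed.

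The cost is wording only: no new data, and a mixed model is already planned. The one small downside is that a mean difference is harder to read if a scale shows a ceiling. The residual check and bootstrap interval show whether the inference is affected.

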#### 1.7.6 Sample Size Estimation

The sample size calculation for this study was calculated based on the primary outcome desire which is willingness for hepatitis C treatment. The sample size calculation will be calculated using the formula for testing the different in proportion between two groups (Lwanga et al., 1991). The formula and calculation are as depicted below:

$$n = \frac{\{[Z_{(1-\alpha/2)} * \sqrt{2\bar{P}(1-\bar{P})}] + [Z_{(1-\beta)} * \sqrt{P_1(1-P_1) + P_2(1-P_2)}]\}^2}{(P_1-P_2)^2}$$

$$n = \frac{\{[1.96 * \sqrt{1.19(1-0.405)}] + [0.842 * \sqrt{0.1875 + 0.2464}]\}^2}{(0.31)^2}$$

$$n = 39$$

Thus, the sample size calculated is equal to 39 for one arm. Total sample size for both control and intervention groups are 78 persons (39 x 2). Following that, an additional adjustment for dropouts were made based on the 77% attrition rate from previous study (Arain et al., 2016). Therefore, the adjustment for response rate is 78/(1-L) (L= attrition rate) = 78/0.33= 236 (118 respondents per arm) (KK Gupta et al., 2016). Thus, the sample size needed for this study is 118 pairs of intervention and control groups which amount to 236 subjects. The information used for sample size calculation is as

presented in Table 3.1. The calculation was based on findings from a randomize control trial study for willingness of hepatitis C treatment (Arain et al., 2016).

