#### 1.10.1 Development of Health Intervention Module

The health intervention module will be developed in Malay language and validated by the supervisory committee and other expert from Universiti Putra Malaysia (UPM) and Malacca State Health Department. The expert will consist of Public Health specialist and Family Medicine Specialist. Figure 3.4 summarize the flow of health education module development.

[figure not shown]

**Figure 3.4. The schematic diagram for the development of the health education module on increasing willingness for hepatitis C treatment**

The intervention will be delivered during MMT client's appointment with the medical officer in charge of the MMT programs in the form of brief intervention module. The medical officer involve with the study will be brief and undergo training on proper way to conduct questionnaire interview and deliver health education intervention module to the clients. Prior to the intervention session, a baseline assessment will be conducted using validated questionnaire to measure their knowledge regarding hepatitis C, attitude towards hepatitis C infection, subjective norm on hepatitis C treatment, perceived behavioural control on hepatitis C treatment and willingness for hepatitis C treatment. Following that, the brief intervention will be deliver face to face by the medical officer in charge using several materials provided by researcher. The estimated duration of the intervention session is around one and half hours. Table 3.2 summarized the application of TPB constructs in the development of the health education intervention module.

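### Neither between-arm analysis of willingness conditions on the baseline answer already collected: both are valid, but power is given away and the GLMM group main effect is diluted

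*Protocol*

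**What the plan says.** Section 1.14.1 makes willingness the primary outcome, and section 1.10.2 and Appendix A record it as a single yes/no item. It is measured before the module is delivered: "Prior to the intervention session, a baseline assessment will be conducted using validated questionnaire" (section 1.10.1), and willingness is among the items listed there. Section 1.13 has both arms assessed at baseline, T1 and T2.

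Section 1.15.1 names two between-arm analyses that apply to this outcome:

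- For categorical data at a given time: "The Chi-square test will be used to compare frequency different of categorical data between intervention and control groups", with Fisher's exact test for sparse 2 by 2 tables.
- Over time, a GLMM "to test the main effect and interaction between and within the intervention and control groups overtime (baseline, immediately post intervention, and 3-month post intervention". Baseline is therefore one of the response times.

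Baseline willingness is nowhere named as a covariate, and it is not among the other associated factors in section 1.14.3. The sample size in section 1.7.6 and Table 3.1 rests on an unadjusted comparison of two proportions at 3 months: 0.75 ("Proportion of respondent willing for treatment in intervention group at 3 months post intervention") against 0.44 ("Proportion of respondent willing for treatment in control group at 3 months post intervention").

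**The concern.** A participant's answer before the intervention is likely to be one of the better predictors of the same answer three months later. The two analyses use it as follows.

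- **Chi-square or Fisher.** Baseline willingness is ignored. A chance imbalance at baseline carries into the 3-month difference in proportion to the correlation.
- **GLMM group-by-time term.** This compares change from baseline. It uses the baseline, but subtracts all of it instead of the part that predicts follow-up, so it is noisier than a comparison conditional on baseline.
- **GLMM group main effect.** Averaged over the three times, it includes a time at which randomisation makes the expected arm difference zero. It understates the effect after the intervention.

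The design plans for few completers (about 39 of 118 per arm), so a few points of power matter, and the information has already been paid for.

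**Working it through.** **Inputs from the protocol.** P1 = 0.75, P2 = 0.44, mean 0.595; Z = 1.96 ("the value of the standard normal distribution corresponding to a significance level of alpha of 0.05 for a two-sided test"); Z = 0.842 ("corresponding to the desired level of power of 80" percent); 39 evaluable per arm ("the sample size calculated is equal to 39 for one arm"); 118 recruited per arm.

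**Assumptions, not in the protocol.** The baseline-to-3-month correlation rho, shown from 0.2 to 0.5; for the simulation only, baseline willingness of 0.44 in both arms. Participants are treated as independent, as in the plan's own formula.

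**Step 1: the plan's figure.**
- 1.96 × √(2 × 0.595 × 0.405) = 1.361
- √(0.1875 + 0.2464) = 0.6587
- n = (1.361 + 0.842 × 0.6587)² / 0.31² = 38.2, so 39 per arm

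This reproduces. (The printed substitution has 1 − 0.405 in place of 1 − 0.595, which would give about 51. The stated 39 is the value with 0.405.)

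**Step 2: power of the unadjusted test.** Inverting the same formula, power = Φ[(0.31 × √n − 1.361) / 0.6587]. At n = 39 this is Φ[(1.936 − 1.361) / 0.6587] = Φ(0.873) = 80.9%.

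**Step 3: the alternatives.** Replace n by 39/f, where f is the variance relative to the unadjusted comparison:
- adjusted for baseline: f = 1 − rho²
- change from baseline, all 118 baselines per arm kept: f = (1 − rho²) + (1 − rho)² × 39/118
- change from baseline, complete pairs only: f = 2(1 − rho)

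Example at rho = 0.5, adjusted: 39/0.75 = 52, and Φ[(0.31 × √52 − 1.361) / 0.6587] = Φ(1.33) = 90.8%.

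| rho | chi-square | adjusted | change, all 118 baselines | change, complete pairs |
|---|---|---|---|---|
| 0.2 | 80.9% | 82.5% | 74.2% | 60.2% |
| 0.3 | 80.9% | 84.5% | 78.0% | 66.2% |
| 0.4 | 80.9% | 87.3% | 82.5% | 73.1% |
| 0.5 | 80.9% | 90.8% | 87.6% | 80.9% |

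The gain over chi-square is 1.6, 3.6, 6.4 and 9.9 points. Against the change contrast with all baselines, at rho 0.3, 0.4 and 0.5, it is 6.5, 4.8 and 3.2 points. The change columns are a linear approximation to the GLMM interaction. No logit GLMM was fitted.

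**Step 4: check with binary data.** In simulated trials of 39 per arm, power was 81% for chi-square against 84% adjusted at a phi of 0.3, 82% against 87% at 0.4, and 82% against 90% at 0.5. The gain is about 3, 5 to 6, and 8 points. With baseline 0.44 and follow-up 0.75, the largest possible phi in the intervention arm is √[(0.44 × 0.25) / (0.56 × 0.75)] = 0.51, so 0.5 is close to the ceiling there.

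**Step 5: dependence on retention, at rho = 0.5.**

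| Completers per arm | chi-square | adjusted |
|---|---|---|
| 27 | 64.8% | 77.6% |
| 39 | 80.9% | 90.8% |
| 60 | 94% | 98% |
| 80 | 98.4% | 99.7% |
| 118 | 99.9% | 100.0% |

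The row of 39 matches the divisor actually used in section 1.7.6 (118 × 0.33 = 38.9). The row of 27 matches the 77% attrition stated there (118 × 0.23 = 27.1). That mismatch is a separate matter.

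**Step 6: the main effect.** With an effect d at both follow-ups and zero at baseline, the average over the three times is (0 + d + d)/3 = 2d/3. No correlation is needed for this. For d = 0.31 it would be about 0.21 on the risk-difference scale.

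**The case against.** The strongest reply is that nothing here is invalid. An unadjusted chi-square test of randomised arms keeps its type I error, chance imbalance included. It matches the formula used for sizing, answers the objective of comparing the arms at each time, and meets the 80% target. The GLMM interaction likewise answers the objective of change within and between groups over time. All of that stands, and it is why this is a point about efficiency and not about error.

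A reader might infer that both analyses lose 8 to 10 points of power at a correlation of 0.5. The documents do not support that. A loss of this size applies to the chi-square test only, and near the highest correlation possible in the intervention arm. The GLMM does not discard the baseline. Section 1.15.2 commits to including everyone randomised, and section 1.8.2 releases the allocation code only after the baseline measurement. All 118 baselines per arm can therefore enter the model, and its loss at 0.5 is about 3 points. The lower complete-pairs figures require dropping the baselines of those lost to follow-up, which the protocol does not say.

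A reader might also infer that the main effect will be reported as the intervention effect. Section 1.15.1 says only that it will be tested, so the dilution is a risk of misreading.

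It can also be said that covariates belong in a statistical analysis plan, which is not shown. That would answer a complaint about missing detail. But the protocol itself selects an unadjusted test and places baseline among the responses, and the point concerns that choice.

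**Conclusion.** The point holds as avoidable inefficiency plus one GLMM term open to misreading. At the planned 39 completers per arm, conditioning on baseline willingness gains roughly 2 to 10 points of power over the chi-square test for correlations of 0.2 to 0.5. Over a GLMM change contrast that keeps every baseline, it gains roughly 3 to 7 points for correlations of 0.3 to 0.5. The adjusted comparison is the most powerful in every row of the table, but the size depends on a correlation that the protocol does not give and on how many participants are retained. It is negligible if most of the 236 are followed up, and larger if only about 27 per arm are. The two-thirds dilution needs no correlation; it needs only an equal effect at both follow-ups. No bias is shown in the chi-square test or in the group-by-time contrast. The change is worth making because it costs almost nothing.

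**What to change.** In section 1.15.1, base the 3-month between-arm comparison of willingness on a logistic model or GLMM with T1 and T2 willingness as outcomes and group, time, group by time and baseline willingness as terms. Alternatively, keep baseline as an outcome but constrain both arms to a common baseline proportion. Report the 3-month marginal risk difference with its 95% CI. State that a group main effect averaged over baseline will not be interpreted as the intervention effect. Keep the unadjusted proportions by arm and time as description.

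The cost is a few sentences and one covariate in a type of model already planned in SPSS, with no new data, participants or staff. The one drawback is that an adjusted odds ratio is a different quantity from the crude one. Reporting the marginal risk difference avoids this.
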